**LIST OF ABBREVIATIONS AND RELEVANT DEFINITIONS**

|                |                                                                                                                                                                                                                                                                                                                                                  |
|----------------|--------------------------------------------------------------------------------------------------------------------------------------------------------------------------------------------------------------------------------------------------------------------------------------------------------------------------------------------------|
| ABR     | ABR form, General Assessment and Registration form, is the application form that is required for submission to the accredited Ethics Committee (In Dutch, ABR = Algemene Beoordeling en Registratie)                                                                                                                                      |
| AE      | Adverse Event                                                                                                                                                                                                                                                                                                                             |
| AR      | Adverse Reaction                                                                                                                                                                                                                                                                                                                          |
| CCMO    | Central Committee on Research Involving Human Subjects; in Dutch: Centrale Commissie Mensgebonden Onderzoek                                                                                                                                                                                                                               |
| CV      | Curriculum Vitae                                                                                                                                                                                                                                                                                                                          |
| DSMB    | Data Safety Monitoring Board                                                                                                                                                                                                                                                                                                              |
| EU      | European Union                                                                                                                                                                                                                                                                                                                            |
| GCP     | Good Clinical Practice                                                                                                                                                                                                                                                                                                                    |
| IB      | Investigator's Brochure                                                                                                                                                                                                                                                                                                                   |
| IC      | Informed Consent                                                                                                                                                                                                                                                                                                                          |
| METC    | Medical research ethics committee (MREC); in Dutch: medisch ethische toetsing commissie (METC)                                                                                                                                                                                                                                            |
| (S)AE   | (Serious) Adverse Event                                                                                                                                                                                                                                                                                                                   |
| Sponsor | The sponsor is the party that commissions the organisation or performance of the research, for example a pharmaceutical company, academic hospital, scientific organisation or investigator. A party that provides funding for a study but does not commission it is not regarded as the sponsor, but referred to as a subsidising party. |
| SUSAR   | Suspected Unexpected Serious Adverse Reaction                                                                                                                                                                                                                                                                                             |
| Wbp     | Personal Data Protection Act (in Dutch: Wet Bescherming Persoonsgegevens)                                                                                                                                                                                                                                                                 |
| WMO     | Medical Research Involving Human Subjects Act (in Dutch: Wet Medisch-wetenschappelijk Onderzoek met Mensen)                                                                                                                                                                                                                               |

## SUMMARY

**Rationale:** When treating older patients with dizziness in primary care, the current diagnosis oriented approach is insufficient. Often, it is not possible to diagnose an underlying disease and even if a disease is diagnosed, therapeutic options are often limited. In this study a prognosis oriented approach for dizziness in older people in primary care will be investigated.

**Objectives:** In this study we want to validate a risk score for chronic dizziness with persistent impairment in older dizzy patients in general practice. Furthermore, we want to investigate the effectiveness of a risk factor-guided, i.e. a prognosis-oriented, intervention for dizzy older patients with a high risk of persistent impairment.

**Study design:** The study protocol consists of two parts. Firstly, we will perform a validation study to externally validate a 7-item risk score for chronic dizziness with persistent impairment. Secondly, we will perform an intervention study, using a cluster controlled clinical trial. In the intervention study we will compare the effectiveness of a targeted intervention for dizzy older patients with a high risk of persistent impairment with usual care during one year of follow-up.

**Study population:** 375 patients aged 65 years or older who consult their general practitioner (GP) for a new episode of dizziness existing for at least one month.

**Intervention:** In older patients with a high risk of persistent impairment because of dizziness we will compare a risk factor-guided intervention consisting of one, two, or three of the following interventions: (1) medication adjustment in case of the usage of  $\geq 3$  Fall Risk Increasing Drugs (FRIDs), (2) stepped care in case of anxiety/depression, and (3) exercise therapy in case of impaired functional mobility. All three interventions are evidence based and usual care for the above-mentioned risk factors.

**Main study parameters/endpoints:** The primary clinical outcome is dizziness related impairment at follow-up, which will be assessed using the Dizziness Handicap Inventory (DHI). Secondary outcomes are quality of life (EQ-5D-5L), difference in 'Fall Risk Increasing Drug' count, anxiety/depression, dizziness frequency, fall frequency, health care utilization.

**Nature and extent of the burden and risks associated with participation, benefit and group relatedness:**

A group of 125 patients of the validation group will receive 3 questionnaires by mail at baseline and at 6 and 12 months follow-up. The group of 250 patients participating in the intervention study will receive four questionnaires at baseline, 3, 6 and 12 months follow-up. All 375 patients will be subjected to a baseline assessment of 30 minutes at their home including a structured interview and execution of the Timed 'up-and-go' test. Patients in the intervention group (n=125) will receive – in addition to usual (general practice) care – a targeted intervention, depending on the presence of specific risk-factors. Patients in the

control group (n=125) and validation group (n=125) will receive (general practice) care as usual. No treatment will be denied to any participants nor will it be postponed. There are no major medical health risks for participants in this study. The experimental group may benefit from the intervention by a reduction of impairment due to dizziness and/or a decrease in dizziness frequency.

## 1. INTRODUCTION AND RATIONALE

Dizziness is one of the 'geriatric giants'. Thirty percent of people above 65 years of age experience some form of dizziness, increasing to 50% in persons above 85. Nine percent of all persons aged 65 years or older visit their general practitioner (GP) at least once a year because of dizziness. The one-year prevalence of dizziness in general practice is higher in women than in men (65+ years: 9.5% vs. 6.8%) and increases with age (65-74: 6.8%, 75-84: 10.2%; 85+: 10.8%). Dizziness can lead to persistent limitations in daily functioning and is associated with worsening of depressive symptoms, self-rated health, and a decrease of social activities. Dizziness is one of the most important symptoms negatively affecting well-being in old age. It is also a major risk factor for falling, leading to (fatal and non-fatal) injuries and high healthcare costs. According to Statistics Netherlands (CBS), the annual number of fall related hospital admissions for persons of 65+ years will increase from 43,000 in 2011 to 73,000 in 2030, fall related emergency visits from 83,000 to 140,000, and corresponding healthcare costs from €820 million to €1,400 million.

Despite the differences in aetiology of dizziness between younger and older patients, guidelines on dizziness advocate the same diagnosis-oriented approach for all patients regardless of their age. However, such an approach is insufficient in older patients presenting with dizziness. Often, it is not possible to identify an underlying cause in dizzy older patients. In 40-80% of dizzy older patients, GPs record a symptom diagnosis as the final diagnosis ('dizziness' or vertigo). Moreover, even if a disease is revealed, therapeutic options are limited. Therefore, the approach of dizziness in older patients has to change. GPs should not just stick to their diagnostic quest, but also pay attention to the prognosis of a dizzy patient: is this patient at risk of an unfavourable outcome and, if so, how to improve this outcome?

Several members of our research group initiated the study Dizziness In Elderly Patients (DIEP) in collaboration with the Department of General Practice of the Academic Medical Center Amsterdam in order to fill the gap of knowledge about dizziness in older patients. This study resulted in more knowledge of epidemiology, aetiology, and diagnosis of dizziness in older patients in general practice. Furthermore, a large cohort study investigating the prognosis of dizzy older patients in general practice recently identified seven risk factors for chronic dizziness with persistent impairment. These risk factors are (1) onset of dizziness more than six months ago, (2) dizziness provoked by standing still, (3) trouble with walking and/or falling as associated symptom, (4) polypharmacy, (5) absence of diabetes, (6) anxiety and/or depressive disorder, and (7) impaired functional mobility. Three

of these risk factors are amenable to treatment: polypharmacy, anxiety and/or depressive disorder, and impaired functional mobility.

The results of this cohort study, combined with previous findings of DIEP, provide the basis of the present research proposal.

The first objective of the proposed study is to externally validate our previously developed 7-item risk score for chronic dizziness with persistent impairment. Although the discriminative ability of our developed risk score was good (area under the receiver operating characteristic curve [AUC] of 0.80), it is necessary to validate prediction models in new individuals before they can be implemented in guidelines or applied in clinical practice. If our risk score confirms our previous findings, GPs will have an accurate, easy-to-use clinical tool to identify dizzy older patients with a poor functional prognosis.

Secondly, we want to demonstrate the effectiveness of a risk factor-guided intervention for treating dizziness in older patients in general practice. This intervention includes medication adjustment, a stepped-care program for anxiety/depression, and physical exercise therapy. If proven effective, GPs will be able to improve the functional prognosis of older patients presenting with dizziness, even when a diagnosis is (still) unavailable. Such an intervention will not only improve patients' perceived health but will also lead to a significant reduction of healthcare costs by decreasing fall rate, morbidity (especially fractures) and healthcare utilization. Although several authorities in the field of dizziness – like Mary Tinetti and Philip Sloane – promote a risk factor guided approach of dizziness in older patients, the effectiveness of such an approach has never been investigated.

## 2. OBJECTIVES

This study aims to investigate if a prognosis-guided clinical strategy is more effective than usual care when treating patients with dizziness in primary care.

### Primary Objectives:

1. To validate a previously developed risk score for dizziness-related impairment in older patients in general practice. The risk score consists of seven predictors: 1) onset of dizziness more than six months ago, 2) dizziness provoked by standing still, 3) trouble with walking and/or falling as associated symptom, 4) polypharmacy, 5) absence of diabetes, 6) anxiety and/or depressive disorder, and 7) impaired functional mobility.
2. To investigate the effectiveness of a risk factor-guided intervention for treating dizzy older patients with a high risk of persistent impairment. The intervention includes medication adjustment, a stepped-care program for anxiety/depression, and physical exercise.

### Secondary Objectives:

1. To investigate if a targeted intervention in older dizzy patients in general practice will reduce dizziness frequency and fall incidence.
2. To assess if health care utilization of older dizzy patients receiving a targeted intervention will decrease compared to older dizzy patients receiving usual care.
3. To investigate if our targeted intervention is cost-effective.
4. To investigate if older dizzy patients with significant dizziness-related impairment have more often an anxiety- or depressive disorder than non-impaired older dizzy patients in general practice.
5. To investigate the course of anxiety and depression in older dizzy patients in general practice during one year of follow-up.

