#### 8.1.2 Secondary study parameters/endpoints (if applicable)

- Quality of life, as measured with the EQ-5D-5L.
- Dizziness frequency, defined as the number of episodes of dizziness per day, week, month and year. Dizziness frequency will be assessed using a calendar filled in by the patient during a 12 month period.
- Difference in FRID count, defined as the difference in FRID count between baseline and after 12 months follow-up.
- Presence of anxiety/depression, as measured with GAD-7, PHQ-PD, and PHQ-9.
- Fall frequency, defined as the number of falls per year. Fall incidence will be assessed using a calendar filled in by the patient during a 12 month period.
- Health care utilization. We will use the extracted data from the electronic medical records of all patients to assess the number of registered medical consultations, prescriptions, referrals, hospital admissions, and nursing home admissions.

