#### Baseline assessment

All patients will be subjected to a baseline assessment of 30 minutes during a home visit or at the surgery of the patient's GP, depending on the preference of the patient and the mobility of the patient. Baseline assessment will be carried out by a physician or a trained research assistant.

The baseline assessment includes a structured interview and the TUG.

*Structured interview.* This includes record of socio-demographic characteristics, intoxications, current medication use, history of falls, dizziness characteristics, and the use of a hearing, seeing or walking aid.

*Timed 'up and go' Test (TUG)*. The TUG will be executed to assess impaired functional mobility. The TUG consists of an observation of the patient rising from a standard arm chair (approximate seat height of 46 cm), walking to a line on the floor 3 meters away, turning, returning, and sitting down again. The subject wears his regular footwear and uses his customary walking aid (none, cane or walker). No physical assistance is given. The patient starts with his/her back against the chair with his/her arms resting on the chair's arms, and his/her walking aid at hand. On the word 'go' the patient gets up and walks at a comfortable and safe pace. The patient will walk through the test once before being timed in order to become familiar with the test. A test score of  $\geq 20$  seconds reflects impaired functional mobility.

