#### *Calendar*

- Dizziness and fall calendar for patients of group B and C (n = 250). At baseline assessment the patient will be handed out a calendar to keep up frequency dizziness and falls for 12 months. The patient will be instructed in the use of keeping up dizziness and fall frequency with the calendar. The patient will be asked to fill out the calendar every week which will take no more than 1 minute weekly.

The following table gives an overview of all measurements and instruments.

| Overview of all measurements and instruments |                  |       |        |                    |       |       |        |
|----------------------------------------------|------------------|-------|--------|--------------------|-------|-------|--------|
|                                              | Validation study |       |        | Intervention study |       |       |        |
|                                              | baseline         | 6 mo. | 12 mo. | baseline           | 3 mo. | 6 mo. | 12 mo. |
| Screening dizziness                          |                  |       |        |                    |       |       |        |
| handicap (DHI-S)                             | x                |       |        | x                  |       |       |        |
| Baseline assessment                          | x                |       |        | x                  |       |       |        |
| Dizziness Handicap (DHI)                     | x                | x     | x      | x                  | x     | x     | x      |
| QoL (EQ-5D-5L)                               | x                | x     | x      | x                  |       | x     | x      |
| Depression (PHQ-9)                           | x                | x     | x      | x                  | x     | x     | x      |
| Anxiety (GAD-7)                              | x                | x     | x      | x                  | x     | x     | x      |
| Panic disorder (PHQ-PD)                      | x                | x     | x      | x                  | x     | x     | x      |
| FRID count                                   | x                |       | x      | x                  |       |       | x      |
| Dizziness and fall frequency (calendar))     |                  |       |        | ----- weekly ----- |       |       |        |

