### 10.2 Secondary study parameter(s)

Presence of anxiety/depression, quality of life, dizziness frequency, fall incidence and health care utilization will be taken along in the univariate and multivariate analysis as stated above.

The economic evaluation will be analysed according to the intention-to-treat principle. Costs typically have a highly skewed distribution. Therefore, bootstrapping with 5000 replications will be used to calculate 95% confidence intervals around the mean difference in total costs between the treatment groups. The effect measure that will be used for the cost-effectiveness is EQ-5D-5L. Incremental cost-effectiveness ratios (ICERs) will be calculated by dividing the difference in mean total costs between the

treatment groups by the difference in mean effects between the treatment groups. Bootstrapping will be used to estimate the uncertainty surrounding the ICERs which will be graphically presented on cost-effectiveness planes. Cost-effectiveness acceptability curves and net monetary benefits will also be calculated. Cost-effectiveness acceptability curves show the probability that the intervention is cost-effective in comparison with usual care for a range of different ceiling ratios thereby showing decision uncertainty.

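### Health care utilization has no stated extraction window and no baseline value, so its comparison between arms cannot be adjusted for prior use unless that is extracted

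*Protocol*

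**What the plan says.** - **Objective (section 2, secondary objective 2).** "To assess if health care utilization of older dizzy patients receiving a targeted intervention will decrease compared to older dizzy patients receiving usual care".
- **Endpoint (8.1.2).** "We will use the extracted data from the electronic medical records of all patients to assess the number of registered medical consultations", and likewise prescriptions, referrals, and admissions to hospital or nursing home. No period is given, before or after baseline. Neighbouring endpoints do have one: dizziness and falls are kept on a calendar for 12 months, and FRID count is "defined as the difference in FRID count between baseline and after 12 months follow-up".
- **Schedule (8.3).** "The following table gives an overview of all measurements and instruments". The table marks a baseline value for the DHI, EQ-5D-5L, PHQ-9, GAD-7, PHQ-PD and FRID count. It has no row for utilization.
- **Baseline interview (8.3).** "This includes record of socio-demographic characteristics, intoxications, current medication use, history of falls, dizziness characteristics", plus the use of aids. Prior use of care is not listed.
- **Analysis (10.1 and 10.2).** "health care utilization will be taken along in the univariate and multivariate analysis as stated above". The analysis referred to is the one in 10.1: univariate and multivariate comparisons, and a repeated-measures mixed model of one-year DHI change with adjustment for confounders that are not named. For costs, 10.2 notes that "Costs typically have a highly skewed distribution" and plans a bootstrapped interval for the difference in mean total costs. It states no baseline adjustment.
- **Allocation and recruitment (8.2 and 11.2).** Practices are randomised before any patient is included, stratified by practice type and disadvantaged area. GPs are then told their allocation. They identify patients during consultations, supplemented by a three-monthly search of their records.

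**The concern.** A patient's own earlier use of care is the natural baseline covariate for later use, and the protocol does not collect it. Two things are at stake.

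**Precision.** If earlier use predicts later use, leaving it out makes the confidence interval for the difference between groups B and C wider than it need be, for utilization and for costs.

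**Protection against imbalance.** With the expected 5 patients per practice, 125 patients per arm means about 125 / 5 = 25 practices per arm. Practices may differ by chance in how often they see, refer and prescribe. Beyond chance, GPs who know their allocation take part in selecting patients, so the two arms may recruit somewhat different people. Prior-year use is the most direct check on such a difference for a utilization endpoint, and the direct means of adjusting for the part of it that shows in prior use.

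**Working it through.** **1. Is a baseline value available anywhere in the plan?** Section 8.1.2 names the source and the items but no dates. The table in 8.3 has no utilization row, and the interview in 8.3 does not ask about earlier care. Sections 10.1 and 10.2 allow covariates, but a covariate must exist before it can enter a model. The main model in 10.1 is for change from a starting value, and utilization has no starting value from which to take a change.

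**2. The plan's own figures.** The protocol gives no mean, standard deviation, correlation or sample size for utilization, so there is nothing to reproduce for this endpoint. The DHI calculation in 4.4 reproduces: 2 × (2.58 + 1.28)² × 19.9² / 12² = 81.9, so 82; 82 × 1.2 = 98.4, so 99; 99 / 0.8 = 123.75, so 124 per arm. Its design effect, 1 + (5 − 1) × 0.05 = 1.2, and its 20% loss are borrowed below. Carrying them over to utilization is an assumption.

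**3. What adjustment could gain.** Further assumptions: a linear model, two-sided alpha of 0.05, and a correlation r between prior-year and follow-up use. The documents give no r, so a range is shown.

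- Effective number per arm: 125 × 0.8 / 1.2 = 83.3.
- Standard error of the difference, in SD units: √(2 / 83.3) = 0.155.
- Difference detectable with 80% power, no prior-use covariate: (1.96 + 0.84) × 0.155 = 0.434 SD.
- With the covariate, the variance is multiplied by 1 − r² and the standard error by √(1 − r²).

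| r | Variance factor | Fall in standard error | Detectable difference | Power at 0.40 SD |
|---|---|---|---|---|
| no covariate | 1 | none | 0.434 SD | 73% |
| 0.3 | 0.91 | 4.6% | 0.414 SD | 77% |
| 0.5 | 0.75 | 13.4% | 0.376 SD | 85% |
| 0.7 | 0.51 | 28.6% | 0.310 SD | 95% |

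The comparison row has no other covariates. If the model already holds variables that predict use, r should be read as the correlation left after those, and the gain is smaller.

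**4. Adjustment, not a change score.** Analysing the change from the prior year multiplies the follow-up-only variance by 2(1 − r): 1.4 at r = 0.3, 1.0 at 0.5 and 0.6 at 0.7. A change score would therefore be less precise than follow-up counts alone when r is below 0.5. Covariate adjustment does not carry that risk.

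**5. Imbalance.** As a hypothetical case, suppose prior-year use differs by 10% between arms, with the same mean and SD in both years. Without adjustment, about r × 10% carries into the follow-up comparison: 3%, 5% or 7% at the three values of r. The documents do not indicate that an imbalance of this size is likely.

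**The case against.** The strongest reply is that much of this is read from silence, and several stronger readings must be set aside.

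- **Unadjusted.** A reader might infer that utilization will be compared without adjustment. The documents do not support that: 10.2 sends it into the multivariate analysis, and 10.1 adjusts for confounders. What stands is that prior use is not among the data collected.
- **Follow-up only.** A reader might infer that only the follow-up year is extracted. The protocol fixes no window at all, so an earlier period is neither planned nor excluded.
- **Unanswerable.** A reader might take the word decrease in objective 2 to require a starting level. The sentence goes on to a comparison with usual care and can be read as a contrast between arms, which follow-up counts from a randomised trial can answer.
- **Indistinguishable from chance.** A reader might say that a chance difference between practices could not be told apart from an effect. An interval that allows for clustering covers chance imbalance, and the stratification helps. Neither covers differences that arise through recruitment.
- **Highly variable counts.** The protocol says only that costs are skewed. It gives no figure for utilization.

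Other parts of the reply carry weight. Current medication is checked against the pharmacist's list for all patients and is a partial baseline for prescriptions. FRID count, the TUG and the questionnaires are proxies for morbidity. Dizziness frequency has no baseline entry in the table either, so utilization is not the only such case. A record extraction needs no visit, which may be why it has no row.

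The choice of covariates may also be left to a statistical analysis plan that is not shown. That does not dispose of the point. Which dates are extracted, and under what consent, is data collection. It belongs in 8.1.2 and 8.3, where it is set out for other endpoints.

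**Conclusion.** The concern holds as a cheap improvement to one secondary objective and to the cost comparison, not as an error that defeats either. The protocol states no extraction window for utilization and provides no baseline value, so adjustment for prior use is impossible unless an earlier period is extracted.

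The loss is one of precision and of protection against imbalance. Its size rests wholly on an assumed correlation: it is small at r = 0.3 (about 5% of the standard error), moderate at 0.5 (about 13%) and substantial at 0.7 (about 29%). These figures come from a linear model with a single r for every item. Skewed, clustered counts will not follow it exactly, and the gain may be smaller for sparse items such as hospital and nursing home admissions. Adjustment would deal with recruitment differences only so far as they show in prior use. That the record holds the year before baseline is a reasonable inference which the documents do not state.

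**What to change.** 1. In 8.1.2, state that the same utilization items are extracted from the record for the 12 months before and the 12 months after each patient's baseline assessment. Confirm with the practices that the record holds the earlier year.
2. Add both windows to the table in 8.3.
3. In 10.2, compare follow-up utilization and costs between groups B and C with the patient's own prior-year value as a covariate, in a model that suits skewed counts and allows for clustering by practice. Do not replace this by a change score. For costs, bootstrap the adjusted difference.
4. Report prior-year use by arm, as a check on recruitment.

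The cost is a longer date range in an extraction already planned for all patients, and consent wording to cover it. There is no extra visit, questionnaire or other burden for patients.
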